### **6.2.3 Day 5, 7, 31, 59 and 87 safety visits conducted by telephone**

On D5, 7, 31, 59 and 87, a telephone interview with subjects will be conducted for AE and concurrent medication reporting.

### **6.2.4 Week 4 in-patient study medication administration visit**

Subjects will be asked to fast for at least 4 hours prior to doing (see section 6.5) and be admitted to the clinic in the morning on D28 (W4). This visit should be performed no more than one day before or one day after the scheduled visit date. Water can be taken *ad libitum*. The following tests will be performed and documented as indicated on the CRF.

#### **6.2.4.1 Pre-dose**

- AE assessment
- a modified physical examination including: (see Section 6.3.1)
  - vital signs
  - body weight
- urine pregnancy test for women of childbearing potential (see Section 6.3.3)
- urine sample for illicit drug screening (see Section 6.3.3)
- concurrent medication assessment (see Section 6.3.1)
- ECG (see Section 6.3.2)
- blood samples for: (see Section 6.3.3)
  - haematology
  - I-Stat system E3+
  - clinical chemistry
  - HIV viral load assessment
  - CD4+ T-cell counts

#### **6.2.4.2 Study medication administration**

- study treatment will be administered as described in Section 7.5.3.2
- upon reinfusion of the study medication, subjects will be under constant medical supervision for at least 3 hours with regular formal medical checks not less than hourly until 8 hours post-treatment.

#### **6.2.4.3 Post-dose**

- Subjects will remain supine or semi-supine for 4 hours post-administration
- At approximately 4 hours post-treatment, a standard meal will be given. After 8 hours food will be provided as required.
- Continuous cardiac monitoring via lead 2 for 4 hours
- ECG (see Section 6.3.2) 4 hours post-administration
- a modified physical examination (see Section 6.3.1) at 30 min, 4 and 24 hours post dose
- vital signs (BP, temperature, heart rate and respiratory rate) will be measured at 15, 30, 45, 60, 75, 90 and 105 min, and 2, 3, 4, 6, 8, 12 and 24 hours after dosing

- Blood samples for: (see Section 6.3.3)
  - haematology at 4 hours post dose
  - clinical chemistry at 4 hours post dose

Subjects remain in the clinic for 24 hours following the administration of study medication. Prior to discharge, subjects will have the following tests performed:

- blood samples for: (see Section 6.3.3)
  - haematology
  - clinical chemistry
- AE and concurrent medication assessments
- vital signs (see Section 6.3.1)

Subjects will be discharged 24 hours post-dose only if the subject is clinically well.

## **6.2.5 Week 8 and 12 in-patient study medication administration visits**

Subjects will be asked to fast for at least 4 hours prior to dosing (see section 6.5) and be admitted to the clinic in the morning on D56 (W8) and D84 (W12) respectively. These visits should be performed no more than one day before or one day after the scheduled visit date. Water can be taken *ad libitum*. The following tests will be performed and documented as indicated on the CRF.

### **6.2.5.1 Pre-dose**

- AE assessment
- a modified physical examination including: (see Section 6.3.1)
  - vital signs
  - body weight
- urine pregnancy test for women of childbearing potential (see Section 6.3.3)
- urine sample for illicit drug screening (see Section 6.3.3)
- concurrent medication assessment (see Section 6.3.1)
- ECG (see Section 6.3.2)
- blood samples for: (see Section 6.3.3)
  - haematology
  - I-Stat system E3+
  - clinical chemistry
  - HIV viral load assessment
  - CD4+ T-cell counts
  - immunogenicity at W12
- blood/serum samples for banking (see Section 6.3.4)

### **6.2.5.2 Study medication administration**

- study treatment will be administered as described in Section 7.5.3.2
- upon reinfusion of the study medication, subjects will be under constant medical supervision for at least 3 hours, with regular formal medical checks not less than hourly until 8 hours post-treatment.

### **6.2.5.3 Post-dose**

- subjects will remain supine or semi-supine for 4 hours post-administration
- at approximately 4 hours post-treatment, a standard meal will be given.
- a modified physical examination (see Section 6.3.1) at 30 min, and 4 hours post dose
- vital signs (BP, temperature, heart rate and respiratory rate) will be measured at 15, 30, 45, 60, 75, 90 and 105 min, and 2, 3, 4, 6 and 8 hours after dosing

- continuous cardiac monitoring via lead 2 for 4 hours
- ECG (see Section 6.3.2) 4 hours post-administration
- blood samples for: (see Section 6.3.3)
  - haematology at 4 hours post dose
  - clinical chemistry at 4 hours post dose

Subjects remain in the clinic for 8 hours following the administration of study medication. Prior to discharge, subjects will have AE, concurrent medication and vital signs assessments (see Section 6.3.1). Subjects will be discharged 8 hours post-dose only if there are no ongoing medical issues requiring further follow up.

### **6.2.6 On-study clinic visits Day 3 and Weeks 2, 6, 10, 13, 14 and 16**

Subjects will return to the clinic for assessments on D3, D42 (W6), D70 (W10), D91 (W13), D98 (W14) and D112 (W16). With the exception of D3, for which there is no visit window, these visits should be performed no more than one day before or one day after the scheduled visit date. The following tests will be performed and documented as indicated on the CRF:

- a modified physical examination will be performed on D3 and W2, 6, 10, 13, 14 and 16 including: (see Section 6.3.1)
  - vital signs
  - body weight
- AE assessment to be performed on D3 and W2, 6, 10, 13, 14 and 16
- concurrent medication assessments to be performed on D3 and W2, 6, 10, 13, 14 and 16
- blood samples for: (see Section 6.3.3)
  - haematology to be performed at W2, 6, 10, 13, 14 and 16
  - clinical chemistry to be performed at W2, 6, 10, 13, 14 and 16
  - CD4+ T-cell counts to be performed at W16
  - HIV-1 Viral load assessment to be performed at W16
  - HIV-1 resistance assessment to be performed at W14 in accordance with clinical care (see Section 6.3)
  - immunogenicity to be performed at W10, 13, 14 and 16
- urine pregnancy test for women of childbearing potential to be performed at W16 (see Section 6.3.3)
- blood/serum samples for banking to be performed at W10, 13, 14 and 16 (see Section 6.3.4)

### **6.2.7 Exit evaluation (Week 24)**

This visit should be performed no more than 3 days before or one day after the scheduled visit date. Subjects will return to the clinic. The following tests will be performed and documented as indicated on the CRF:

- a full physical examination including: (see Section 6.3.1)
  - vital signs
  - body weight
- AE assessment
- concurrent medication assessments (see Section 6.3.1)
- blood samples for: (see Section 6.3.3)
  - haematology
  - clinical chemistry
  - CD4+ T-cell counts
  - HIV-1 Viral load assessment (in accordance with clinical care, see Section 6.3)
- urine pregnancy test for women of childbearing potential (see Section 6.3.3)

## 6.3 Details on Scheduled Assessments

### 6.3.1 Demographic Data, Medical History, Physical Examination, Vital Signs

Demographic data will include sex, ethnicity and date of birth. The medical history will include any diagnosed and/or recurrent medical conditions, and any medications/medical procedures currently ongoing, including non-prescription medication, will be recorded in the CRF.

A complete physical examination (including head, ears, nose, throat, lungs, lymph nodes, heart, abdomen and skin) will be conducted at Screening to determine study eligibility. A complete physical examination will also be conducted at the exit visit (W24) or at the early termination visit if applicable. At other scheduled visits, a full physical examination is recommended if, in the opinion of the Investigator, any clinical changes are suggested by the subject's interim clinical history.

A modified physical examination will be performed at all other scheduled clinic visits. This modified physical examination will be performed to document physical findings of systems appropriate to assessing the clinical status of the disease process.

Vital signs will be measured at every scheduled clinic visit and at the early termination visit if applicable. Vital signs will be measured by:

- body temperature (degrees Celsius [°C])
- respiratory rate (breaths/min)
- pulse rate (beats/min),
- BP (mm mercury [mmHg])

BP and pulse are to be recorded after the subject has been semi-supine for at least 10 minutes. These parameters should be measured when the subject is rested sufficiently. Refer to the Study Reference Manual for more details of the methods to be used.

Vital signs will also be measured at other times if deemed clinically appropriate.

Body weight (kg, without shoes) will be measured at Screening, Baseline, W4, 8, 12, 16 and 24 and at the early termination visit if applicable.

Height (centimetres [cm], without shoes) will be measured and documented at the Screening visit.

### 6.3.2 Electrocardiograms

The 12-lead electrocardiogram (ECG) recordings in this clinical trial will be performed in a standardised manner as outlined in the Study Reference Manual. Repeat measurements will be performed if there are any clinical abnormalities observed or artefacts are present. All 12-lead ECG recordings will be reviewed by the Investigator or nominee in real time.

The 12-lead ECG recordings will be performed once the subject has been semi-supine for at least 10 minutes and will be measured in triplicate over approximately 3 minutes. The mean of the triplicate readings will be used to determine eligibility for the study. ECG data must be reviewed by the Investigator or nominee prior to dosing to ensure that each subject has no clinically relevant findings on ECG prior to dosing.

Continuous cardiac monitoring of each subject will be performed on dosing days until 4 hours post-dose and an ECG recorded at approximately 30 min pre-dose and 4 hours post-dose. A 12-lead ECG will be performed for any out of range or arrhythmia alarms deemed clinically significant by the Investigator. Any clinically significant out of range or arrhythmia alarms will be printed out and recorded in the subject's CRF and reported as AEs.

### 6.3.3 Blood and Urine samples for laboratory tests

Blood will be collected at all scheduled clinic visits (and at the early termination visit if applicable) for the tests specified in Table 2 at the times specified in Section 6.2. The times the samples are actually taken will be recorded. All times must be recorded in the 24 hour format.

**Table 2: Laboratory Parameters**

| Test                       | Parameters                                                                                                                                                                                                                                                                                                                                                 |
|----------------------------|------------------------------------------------------------------------------------------------------------------------------------------------------------------------------------------------------------------------------------------------------------------------------------------------------------------------------------------------------------|
| Haematology:               | Haemoglobin, haematocrit, RBC and RBC morphology, WBC and differential WBC count, platelet count, mean corpuscular volume, mean corpuscular haemoglobin concentration, prothrombin time.                                                                                                                                                                   |
| I-Stat system:             | Sodium, potassium, haemoglobin and haematocrit pre-dose on W4, 8 and 12.                                                                                                                                                                                                                                                                                   |
| Chemistry:                 | Sodium, potassium, chloride, bicarbonate, blood urea nitrogen, creatinine, total protein, albumin, serum amylase, serum lipase, phosphate, AST, ALT, gamma glutamyl transferase, alkaline phosphatase, total bilirubin, glucose, creatine phosphokinase, calcium and uric acid levels. Ferritin, Vitamin B12 and serum folate will be tested at Screening. |
| Serology:                  | HIV (unless previously performed), HCV antibody and HBsAg (at screening only).                                                                                                                                                                                                                                                                             |
| HCV RNA:                   | HCV RNA to be tested if HCV antibody is positive (at Screening only)                                                                                                                                                                                                                                                                                       |
| HIV viral load:            | Serum samples will be collected for HIV RNA viral load testing at Screening, Baseline, W4, 8, 12, 16, and 24/Early termination                                                                                                                                                                                                                             |
| HIV Resistance assessment: | Blood will be collected for a HIV resistance assessment if the subject has measurable viral load in accordance with standard clinical care.                                                                                                                                                                                                                |
| CD4+ T-cell counts:        | Blood will be collected for CD4+ T-cell counts at Screening, Baseline, W4, 8, 12, 16, and 24/Early termination.                                                                                                                                                                                                                                            |
| Immunogenicity:            | Blood will be collected at Baseline, W10, 12, 13, 14 and 16. Immunogenicity will be assessed by ELISpot and other immunological assays.                                                                                                                                                                                                                    |
| Plasma Banking:            | A portion of the sample (at least 5 aliquots of 1 mL) at Baseline, W10, 12, 13, 14 and 16 will be banked for exploratory analyses. Plasma will be collected from blood samples for immunogenicity.                                                                                                                                                         |

Urine samples will be collected from women of child bearing potential at Screening, Baseline, W4, 8, 12, 16, and 24/Early termination for pregnancy testing.

Urine samples will be collected from all subjects at Screening, Baseline, W4, 8 and 12 for illicit drug testing.

### 6.3.4 Handling and processing of biological specimens

Blood and urine specimens collected during the trial will contain HIV-1 and possibly other pathogens. All personnel involved in collecting and handling biological specimens should follow appropriate precautionary procedures for handling biohazardous materials as currently recommended by the national regulatory authority. The processing of all biological specimens will be in accordance with relevant written Standard Operating Procedures (SOPs).

Further details of the handling of blood samples can be found in the Study Reference Manual.

### 6.3.5 Time of blood incubation and infusion activities

The time taken for the steps of blood incubation and/or infusion should be recorded.

#### **6.4 Visit windows**

Subjects should attend clinic visits on the days specified. Visits on W2 (D14), W4 (D28), W8 (D56), W12 (D84), W14 (D96) and W16 (D112) should occur within -1 day to +1 day of the scheduled day. The W24 visit should occur within -3 days to +1 day of the scheduled day. There will be no visit window for safety visits conducted via telephone on D5, D7, D31, D59 and D87.

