| Clinical procedures / assessments:      | Refer to Table 1                                                                                                                                                                                                                                                                                                                                                                                                                                                                                                                                                                                                                                                                                                                                                                                                                                                                                                |
| Specialised analyses:                   | 
T-cell immunogenicity will be primarily assessed by interferon gamma Enzyme-Linked Immunosorbent Spot assay (ELISpot) at Baseline and W13 and 14 (1 and 2 weeks after the last vaccination). Peptides assessed will be pools of 15mers overlapping by 11 amino acids and spanning C clade Gag Durban Consensus sequence.
 
Other exploratory immunological assays may be performed (such as viral suppression and intracellular cytokine staining).
                                                                                                                                                                                                                                                                                                                                                                                                                                                 |

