### 4.2 Dosing Regimens

After screening, subjects will be randomised to the following treatment regimens, starting with the lowest dose (1) and escalating to the highest dose (3):

1. 12 mg Opal-HIV-Gag(c) (n=6) or placebo (n=3)
2. 24 mg Opal-HIV-Gag(c) (n=6) or placebo (n=3)
3. 48 mg Opal-HIV-Gag(c) (n=6) or placebo (n=3)

Within each dose cohort, there will be an initial sentinel cohort of 2 subjects who will be randomised sequentially on a 1:1 basis to receive Opal-HIV-Gag(c) or placebo. The remainder of subjects will be randomised no sooner than 2 days after randomisation of the sentinel subjects.

Subjects will be stratified based on clade of infection. There will be a minimum of 5 clade C subjects per cohort, with the remaining 4 subjects being any clade. The 2 sentinel subjects in each cohort must

be clade C. After the sentinel dosing, the next 3 clade C subjects will be randomised 2:1, and the remaining 4 subjects (of any clade) randomised 3:1.

All subjects will receive a total of 4 immunisations; at D0, 28 (W4), 56 (W8) and 84 (W12). Immunogenicity will be assessed at D0, 70 (W10), 84 (W12), 91 (W13), 98 (W14) and 112 (W16) and all subjects will be followed until W24.

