## 12.6 Analyses

### 12.6.1 Week 14 Interim Analysis

A planned interim analysis of safety and immunogenicity data will be conducted when all randomised study participants have reached W14. All randomised subjects will have received all IMP administrations and will have completed two weeks follow-up or have permanently withdrawn from the study. There is no intent to stop the study early since the W24 efficacy and safety data are also of interest. A study report will be prepared to present the study results of the W14 analysis.

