### **12.6.5 Analysis of efficacy**

Efficacy is being assessed through the measurement of T-cell immunogenicity. For each variable, summary tables will be produced by time point and by dose level, and may be presented by clade. If appropriate, data will be summarised after log transformation. This will be described fully in the SAP. In addition, summary tables of the number (and percentage) of subjects with viral load and CD4+ T-cell counts will be presented by time point and by dose, and may be presented by clade. All data will be listed.

Immunogenicity of the immunotherapy will be determined based on comparisons between study treatment groups at W14. Changes in efficacy endpoints between the study treatment groups over the entire follow-up period may be the subject of informal statistical analyses which may involve post-hoc calculation of confidence intervals in order to further describe and characterise endpoints of interest. Analyses will compare study treatment groups at each time-point over the entire 24 week follow-up period in terms of appropriate summary statistics. Exploratory analyses will be used to examine the relationship between primary and secondary immunogenic endpoints.

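### Section 6.4 schedules the Week 14 visit on D96; Sections 4.2 and 6.2.6 schedule it on D98, and the two visit windows share only one day

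*Protocol*

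**What the plan says.** Section 6.4 (Visit windows) lists clinic visits by week and day and attaches a tolerance to them. For the visits at issue it reads: "W14 (D96) and W16 (D112) should occur within -1 day to +1 day of the scheduled day". Taken as written, Week 14 may be held on D95, D96 or D97.

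Two other operative sections give a different day:

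- Section 4.2 (Dosing Regimens): "Immunogenicity will be assessed at D0, 70 (W10), 84 (W12), 91 (W13), 98 (W14) and 112 (W16".
- Section 6.2.6 (On-study clinic visits): "Subjects will return to the clinic for assessments on D3, D42 (W6), D70 (W10), D91 (W13), D98 (W14) and D112 (W16". Apart from D3, which has no window, it adds that "these visits should be performed no more than one day before or one day after the scheduled visit date". For Week 14 this gives D97, D98 or D99.

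Two further places fix Week 14 relative to the last dose, which Section 4.2 schedules on D84 (Week 12). The synopsis, under specialised analyses, has ELISpot "at Baseline and W13 and 14 (1 and 2 weeks after the last vaccination". Section 12.6.1 says that subjects at the Week 14 interim analysis "will have received all IMP administrations and will have completed two weeks follow-up", unless they have permanently withdrawn.

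The use made of the visit is stated in Section 12.6.5: "Immunogenicity of the immunotherapy will be determined based on comparisons between study treatment groups at W14". The amendment appendices do not touch the D96 figure, and nothing in the protocol ranks Section 6.4 against Sections 4.2 and 6.2.6.

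**The concern.** A section headed as the rule on visit windows is where site staff and monitors would look up whether a visit is on time. For Week 14 that rule is centred on a day that two other sections contradict. A subject seen exactly on the D98 of Section 6.2.6 is late under Section 6.4; a subject seen exactly on the D96 of Section 6.4 is early under Section 6.2.6. Section 6.2 requires protocol deviations to be recorded and notified to the sponsor, so the mismatch can produce deviations that are not real, or let a sample taken 12 days after the dose pass as on schedule.

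The visit affected is the main immunogenicity time point, both in the synopsis and in Section 12.6.5. The interval from the last dose is part of what defines that measurement. The macaque study described as item 5 of Section 2.3.2 reports peak T-cell responses two weeks after the final treatment, so a two-week interval is the natural target and not an arbitrary label.

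**Working it through.** **Inputs**

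- Week 14 in Section 6.4: D96, tolerance one day either side.
- Week 14 in Section 4.2: D98. In Section 6.2.6: D98, tolerance one day either side.
- Last dose: D84 (Section 4.2). Section 6.2.5 on the Week 8 and 12 dosing visits: "These visits should be performed no more than one day before or one day after the scheduled visit date". The Week 12 dose may therefore fall on D83, D84 or D85.

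**Step 1: which day is right.** The schedule follows day = 7 x week. Applied to every week that Section 6.4 pairs with a day:

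| Week | 7 x week | Day in Section 6.4 | Agrees |
|---|---|---|---|
| 2 | 14 | 14 | yes |
| 4 | 28 | 28 | yes |
| 8 | 56 | 56 | yes |
| 12 | 84 | 84 | yes |
| 14 | 98 | 96 | no |
| 16 | 112 | 112 | yes |

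The days in Section 6.2.6 for Weeks 6, 10 and 13 (42, 70 and 91) follow the same rule. Two weeks after the D84 dose is 84 + 14 = 98. D96 is the figure that does not fit.

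**Step 2: overlap of the windows.** Section 6.4: 96 - 1 to 96 + 1 = D95-D97. Section 6.2.6: 98 - 1 to 98 + 1 = D97-D99. Together they cover five days (D95 to D99), of which only D97 lies in both.

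**Step 3: nominal time since the last dose.** Section 6.4: 96 - 84 = 12 days. Section 6.2.6: 98 - 84 = 14 days. The difference is 2 days.

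**Step 4: permitted range of time since the last dose.** The shortest interval is the earliest visit minus the latest dose (D85). The longest is the latest visit minus the earliest dose (D83).

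| Window followed | Shortest | Longest | Spread |
|---|---|---|---|
| Section 6.4 only | 95 - 85 = 10 days | 97 - 83 = 14 days | 4 days |
| Section 6.2.6 only | 97 - 85 = 12 days | 99 - 83 = 16 days | 4 days |
| Both in use | 95 - 85 = 10 days | 99 - 83 = 16 days | 6 days |

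**The case against.** The best answer is that a careful reader would not be misled. The visit is called Week 14 throughout, two sections state D98 outright, two more imply it, and only one figure disagrees. Section 6.2.6 also places its own correct window beside the list of Week 14 procedures. This stands as far as intent goes: there is no real doubt that D98 was meant. It does not remove the conflict between two operative window rules, and a window should not have to be inferred.

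Second, the consequences are conditional and small. Nothing shows that any visit was mistimed. The 10-to-16-day range is reached only when the extremes of both the dosing and the visit windows coincide, and the intended windows alone already allow a 4-day spread. The analysis is descriptive (Section 12.1), efficacy uses all randomised subjects, and no stated rule excludes out-of-window samples. Treatment is randomised and blinded, so there is no evident reason for timing slips to differ between active and placebo within a cohort. Blood for immunogenicity is also taken at Weeks 10, 12, 13 and 16. All of this stands, and it is why the point is rated minor.

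Third, D96 appears once and differs from D98 by a single digit, so a look at the signed protocol is sensible before amending. The surrounding days in the same sentence are intact, and there is no positive sign of a reading error.

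Section 6.4 also omits Weeks 6, 10 and 13, which Section 6.2.6 covers, while Section 6.4 supplies a day for Week 2 that the day list in Section 6.2.6 lacks. That is not a conflict; it only suggests that the two lists were never reconciled.

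**Conclusion.** The concern holds. D96 in Section 6.4 is a wrong figure in an operative rule; the correct day is D98, with a window of D97-D99. The error moves the nominal Week 14 sample from 14 to 12 days after the last dose and leaves one day common to the two windows. If both were applied, the permitted interval after the last dose would widen from 12-16 to 10-16 days. These ranges assume only the one-day tolerances stated for the Week 12 and Week 14 visits. Whether any subject was affected cannot be told from the protocol.

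Severity is minor. Week 13 (D91), the dosing schedule, the sample size and the primary safety objective are untouched. What is at stake is clean timing and correct deviation logging at the visit on which a secondary objective mainly rests.

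**What to change.** In Section 6.4, change D96 to D98, so that Week 14 is D98 with window D97-D99 throughout, and notify the site. Listing Weeks 6, 10 and 13 in Section 6.4 at the same time would align it with Section 6.2.6, but is optional. Any Week 14 visit already held on D95 or D96 should carry its actual date; Section 6.3.3 already requires the actual sampling times to be recorded, so no new data collection is needed. The cost is one number in the protocol and a note to a single centre.
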